### Data collection

#### Baseline surveys

The staff changes after randomisation resulted in 185 educators from the 41 intervention schools and 167 from the 35 usual care schools participating at baseline (See Figure
2a). At baseline there were a total of 728 adolescent participants in the study, 425 in the intervention group and 303 receiving usual care (See Figure
2b). After intensive follow-up we achieved a response rate of 64.5% (n = 352) for educator and 81.5% (n = 728) for carer surveys. Information was obtained directly from schools on intellectual functioning for 203 of the adolescents.

#### Qualitative interviews

Individual interviews were conducted with nine special school teachers and four special education unit teachers. A group interview was conducted with three teachers from one special education unit. Sixteen adolescents and their carers were interviewed with only eight carers reporting that they had received a diary from school. All participants interviewed had done the CHAP as requested.

#### Exit surveys

Seventy-four (57.4%) of the 129 teacher exit surveys mailed were returned for analysis (See Figure
2a). Only 26 teachers reported that they began teaching the project in Term 1; 34 did not do so until Term 2; and others began even later in the year. Teachers also differed in the number of hours per week and the number of weeks taught. 47 teachers taught for one semester only, 23 taught over 2 semesters and 4 taught over 3 semesters. On average teachers taught for 11 weeks (SD = 7) and for 57 minutes per week (SD = 28).

Most diaries were not sent home from schools until June/July 2007, but others were not sent until third or in at least two cases fourth term. CHAP booklets were sent to carers of the intervention participants after all schools reported that the diaries had been sent home so that they might take their child to their doctor for the health check in November 2007. These delays required a revision of the original project timeline (Figure
1). Figure
3 shows the actual timeline.

Between Baseline and the Exit many participants were lost to follow up and 41 had no consenting GP so could not continue in the study. Of the 347 adolescents from the intervention group who completed the baseline survey, only 176 returned their CHAP booklets. Of the 486 carer exit surveys sent out in July 2009, 388 (79.8%) were returned (See Figure
4).

**Figure 3 F3:**
[figure not shown]
Actual Project Timeline.

**Figure 4 F4:**
[figure not shown]
Participant Flow – Carer Exit Survey.

##### Health outcome data

GP records were collected for 436 of the participants (See Figure
5). Depending on the time of collection and whether or not all GPs the adolescent had attended during the period had consented to participate in the study, data is available for each participant for a period up to 54 months between January 2006 and June 2010. Data was obtained for 195 of the usual care group, 161 of the intervention group who had completed both the educational and medical components of the intervention and 80 who had the educational intervention only, i.e. they did not do the CHAP.

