#### Health outcome data

In September 2009 we began the process of collecting data from the participants’ usual GPs. A letter was sent to each practice manager advising them of our wish to come and collect the data. We requested copies of all medical records, including correspondence and results of investigations from January 2006 to date of contact with the practice. Approximately one week later this was followed up with a phone call to the practice manager and a date set for data collection. For security reasons, the data were collected from practices by project staff rather than being posted or faxed. Most practice records were computerised and practice managers or doctors produced a print-out of all the data which we collected. In non-computerised practices, photocopies of files were obtained if possible.

Data on medical disorders recorded, past and family histories, allergies, smoking and alcohol consumption, immunisations, current medications, health screening, traumatic injuries, hospitalisations, weight management and the use of the diary was extracted from the notes provided by the GPs. The diagnosed medical disorder was then coded according to both the International Statistical Classification of Diseases and Related Health Conditions (ICD-10) and the International Classification of Primary Care (ICPC-2-R) systems. If there was no diagnosis made, the presenting symptoms were coded. New diagnoses were then identified. A medical professional with extensive experience in the field of intellectual disability checked all ICD codes and new diagnoses. Challenging behaviour is a major issue in this population and much data was available in the GP records collected. All reported challenging behaviours as defined by Emerson
[26] were recorded. The data extraction process was refined from study methods successfully used in other projects conducted by the research team
[6,7]. Although we attempted to mask data extractors to a participant’s treatment status, in practice this was not wholly successful as in many cases the GP had recorded in the notes that his patient had attended his surgery for a CHAP. In a previous research project where the same data extraction tool was used, no difference was found when comparable patterns of health actions were recorded for individuals who received the CHAP regardless of whether or not the extractor was masked
[6].

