#### Quantitative

Percentages of detection of health screenings and health promotion activities initiated, and responses to postal questionnaires will be compared between the intervention and the usual care group using data extracted from medical records. The individual will be the unit of analysis. For continuous outcome variables, a mixed-effects linear regression model will be used to compare the outcomes between comparison groups, with allowance made for cluster and matching effects. For categorical outcomes, a mixed-effects logistic regression model will be used. Sub-group analysis of adolescents at particular risk, such as those with Down syndrome will also be performed.

The primary analyses will be based on the ‘intention-to-treat’ (ITT) principle; all individuals with evaluable data for the outcome under investigation will be analyzed in the group they were randomized to, regardless of treatment received. Additionally, ‘per protocol’ (PP) analyses will be conducted where there have been large deviations from the planned intervention; all individuals with evaluable data for the outcome under investigation will be analyzed according to the treatment received. Any such analyses will be clearly labeled as such and cautiously interpreted as perhaps indicating the maximum theoretical potential of these programs. The PP analyses will consist of three comparison groups according to the timing of the treatment received. The three groups are ‘intervention early’, ‘intervention late’, and ‘no intervention’. The ‘intervention early’ group will consist of individuals whose teachers reported they received their *Ask Health Diary* at the time they were scheduled to, or within 3 months of the time they were scheduled to, and parents/carers confirmed this had been received. The ‘intervention late’ group will consist of individuals who teachers reported they received their *Ask Health Diary* at least three months later than they were scheduled to and those who, when their parents/carers were contacted in July 2008, reported they had not received a diary. The ‘usual care’ group will consist of individuals randomized not to receive an intervention. The separate effects of the CHAP health check, the *Ask Health Diary* and the *Ask Project Curriculum Strategy Booklet* will be explored by comparing outcomes for individuals according to the number, and timing, of components of the health intervention package they received.

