### Intervention

The program was scheduled to be taught in schools in the first term of 2007, but changes in the way teachers were allocated to schools at the beginning of that year meant that in first term there were major staff changes and, as a result, after randomisation but before we had sent out baseline surveys, we saw nine schools withdraw from the study. All schools reported difficulty in obtaining student consent, but more usual care schools than intervention schools withdrew from the study (See Figures
2a and
2b). New teachers in special education units randomised to the intervention group considered it appropriate to teach the program to incoming Grade 8 students which resulted in the inclusion of 12 year old adolescents in the study. Because of the organisational structure of special schools, some even younger students were also included which led to the revision of our age eligibility criteria to 10–18.

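### GP-record outcomes are to be compared as percentages by logistic regression, on records that start about 16 months before baseline and differ in length, with no common post-baseline window or allowance for time observed stated

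*Protocol article*

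**What the plan says.** Under Methods/Design, Health outcome data, practices were asked for all records "from January 2006 to date of contact with the practice". Collection did not take place on one date: "In September 2009 we began the process of collecting data". Under Results, Health outcome data, the article says that "data is available for each participant for a period up to 54 months between January 2006 and June 2010", and gives two reasons for the variation: "Depending on the time of collection and whether or not all GPs the adolescent had attended during the period had consented" to take part. Records were obtained for 436 participants: 195 usual care and 161 + 80 = 241 intervention.

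The intervention came well after January 2006. Under Results, Intervention: "The program was scheduled to be taught in schools in the first term of 2007". Under Results, Exit surveys: "Most diaries were not sent home from schools until June/July 2007", and CHAP booklets went to carers later so that they could "take their child to their doctor for the health check in November 2007".

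The Quantitative section compares "Percentages of detection of health screenings and health promotion activities initiated" between the arms, with the individual as unit of analysis. Categorical outcomes get a mixed-effects logistic model. Clustering and matching are the only adjustments named, and they are named in the sentence on continuous outcomes. Entry to the intention-to-treat analysis requires evaluable data for the outcome; no start date, end date or minimum record length is given.

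**The concern.** A cumulative percentage has a meaning only over a stated period, and an ordinary logistic model treats a 44-month record and a 54-month record as the same amount of observation. The article reports that observation time is unequal and why, yet the analysis it describes does not respond to this.

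Two separate things are at stake. First, an event dated before the intervention cannot be caused by it; counting such events adds the same background to both arms and shrinks the contrast. Second, a longer or fuller record shows more activity whatever the arm. If record length differed between arms, the difference would enter the treatment comparison; if it did not, the result would be noise or attenuation. The article also leaves a useful resource without a stated role: the pre-baseline records already in hand could serve as a covariate.

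**Working it through.** **Dates.** The Data collection section puts carer exit surveys 26 months after baseline, and Results, Exit surveys, dates them to July 2009. Baseline was therefore about May 2007 (inferred; the article does not state it). January 2006 to May 2007 is 16 months. January 2006 to the November 2007 health check is 22 months. Records collected in September 2009 span about 44 months, and those running to June 2010 span 54. Extraction at 28 months after baseline falls in September 2009, which agrees with the stated start of collection.

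**The plan's own figure.** The Sample size section assumes 500 per arm, 20 per school and an ICC of 0.03. Design effect = 1 + 19 × 0.03 = 1.57; effective n = 500/1.57 = 318.5 per arm. For 10% v 19%, two-sided 5% assumed, power is 0.899, which reproduces the stated 90%. No time window is attached to the 10%.

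**Illustration at the achieved sample size.** Assumptions, not document figures:
- Background risk of 10% per 12 months, constant: monthly hazard h0 = −ln(0.90)/12 = 0.00878.
- The intervention raises one 12-month period to 19%: h1 = −ln(0.81)/12 = 0.01756.
- Design effect about 1.14, from 1 + (195/35 − 1) × 0.03, using the 35 usual care schools at baseline. Effective n = 195/1.14 = 171 and 241/1.14 = 211.

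Risk over t months is 1 − exp(−h0·t) under usual care and 1 − exp(−h0·(t − 12) − h1·12) under intervention. Power = Φ[(difference − 1.96 × pooled SE)/unpooled SE].

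| Period counted | Usual care | Intervention | Difference (points) | Power |
|---|---|---|---|---|
| Whole record, 54 months | 37.8% | 44.0% | 6.2 | about 23% |
| Baseline to end of record, 54 − 16 = 38 months | 28.4% | 35.5% | 7.2 | about 32% |
| Baseline to 28 months | 21.8% | 29.6% | 7.8 | about 41% |
| 12 months only | 10% | 19% | 9.0 | about 69% |

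For the first row, pooled SE = 0.0507 and unpooled SE = 0.0504, so (0.0622 − 0.0993)/0.0504 = −0.74 and Φ = 0.23. For the third, pooled SE = 0.0452 and unpooled SE = 0.0446, so (0.0782 − 0.0886)/0.0446 = −0.23 and Φ = 0.41.

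**A second model.** Take 10% v 19% as the risk over the whole post-intervention period, at the planned sample size, and add 13 to 22 pre-intervention months at the control rate to records of 44 to 54 months in all. The percentages become 13.0% v 21.7% at the mildest and 19.0% v 27.1% at the worst. The odds ratio falls from 2.11 to 1.86 or 1.58, and power from 90% to 83% or 68%. The direction is the same and the size depends on the model.

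**Record length with no true effect.** On the 10%-per-12-months hazard, 44 months gives 32.0% and 54 months 37.8%. That gap of about 6 points arises between arms only if every record in one arm stops at 44 months and every record in the other at 54. A mean gap of one month gives about 0.5 points. With equal mean lengths in the two arms, the calculation gives no bias.

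**The case against.** The strongest reply is that the 54-month statement is about availability. It stands under Results and describes what was retrieved; the Quantitative section nowhere says that outcomes are counted from January 2006. Earlier records are needed as look-back to decide whether a diagnosis is new, and the article says that new diagnoses were identified after coding. It also places extraction relative to baseline. A reader might infer that the compared percentages cover the full record; the documents do not support that, and counting pre-intervention events is arguably the less natural reading. This stands, so the dilution is conditional. It does not close the point: placing extraction at 28 months dates the extraction rather than the events, what counts as new is undated, and the idea of a new diagnosis does not settle the window for screening or immunisation.

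A reader might also infer that record length will pass for a treatment effect. No length or collection date by arm is reported, and neither cause of variation is tied to arm. Retrieval did differ, 241/425 = 57% v 195/303 = 64%, but retrieval is not length. It makes a difference possible without showing one.

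Lastly, outcome windows are often left to an analysis plan, and one may exist that is not shown. That is fair as to the missing window. The point rests on what the article does fix: a percentage and a logistic model, for records that it describes as unequal.

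**Conclusion.** The point holds as a weakness in the stated analysis method, not as a demonstrated bias. The model described ignores unequal observation time that the article itself reports, and pre-baseline records already collected are given no stated use as a covariate.

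If the whole record were counted, the illustration puts power at about 23%, against about 41% for baseline to 28 months. Of that gain, removing the 16 pre-baseline months accounts for the step from about 23% to 32%; ending at a common date gives the rest. It would be wrong to read the 69% for a 12-month window as what the fix restores. All of these figures rest on the assumed constant 10% per 12 months, a single 12-month period of benefit, the inferred May 2007 baseline and a design effect of about 1.14. The second model gives a milder loss, from 90% to between 68% and 83% at the planned size. The effect of record length cannot be sized without lengths by arm.

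**What to change.** For the primary analysis of GP-record outcomes:
- Count only events dated from baseline to one common calendar date in both arms, for example 28 months (September 2009), when collection began. State the baseline date used, since it is only inferable now.
- Adjust for whether the same activity was recorded between January 2006 and baseline.
- Where GP coverage is partial, use a complementary log-log or Poisson model with log(months observed) as offset and with school and pair effects. Such an offset does not carry its usual meaning in a logit model.
- Report months observed by arm, so that readers can see whether record length is balanced.

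The analysis is described in the future tense and the records are already extracted, so the cost is wording and date filters. Events after the common date move to a secondary analysis, which gives up some usable follow-up in the primary one.

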**Figure 5 F5:**
[figure not shown]
Participant Flow – GP Data Collection.

## Discussion

We describe the methodology employed that enabled us to perform a pilot and randomised controlled trial involving a hard-to-reach population in a complex naturalistic setting. Although we were required to modify the original protocol due to the nature of this population and the research environment, we maintained the integrity of the study. While our aim was to recruit 1000 participants, the sample size of 728 was still large and good response rates were obtained from both carers and GPs.

Our research strategy was based on our experience of trials in this population and the known barriers to conducting research in adults with intellectual disability. We used materials developed or informed by the previous randomised controlled trials in adults, such as CHAP booklets that have been demonstrated to be acceptable to people with intellectual disability and their families. We believe our success was also based on our awareness that decision-making in government departments and schools can be a political process
[29]. Our approach involved active communication and the development of relationships with all levels of the education system. We met with several tiers of governance in the Queensland Education Department to inform them and gain their support before accessing the schools and teachers. To maximise their understanding of the project, we provided direct contact and accessible written information. At all levels we attempted to convince staff that this project should be included in an already overcrowded curriculum. Prevention programs inevitably place extra burdens on school and student respondents
[30], so in order to encourage participation, schools were reimbursed for staff time. We persisted with reminders and consistent follow-up with school principals, senior, and classroom based, teaching staff. This approach appears to have diminished the known barriers and increased our ability to implement the research protocol.

There were also approaches we took which did not work as well as anticipated. We found a successful pilot project did not provide sufficient breadth of understanding of the usual situation in the school system to adequately inform the larger project. The principal in our pilot special school was enthusiastic, energetic and organised, characteristics found to aid implementation of school-based prevention programs
[31]. These qualities were not always present in liaison staff from other schools. Furthermore, pilot study teacher interviews suggested the project should be conducted in Term 1, but in hindsight other schools may have found it easier to incorporate it into the curriculum mid-year. If the pilot had been conducted in a special-education unit as well as this special school, we may have been better prepared for the recruitment and implementation difficulties that followed. We developed a DVD designed to assist those parents who might have trouble understanding the written material. This approach appeared to assist in recruitment in the special school setting, but anecdotal reports from special education units indicated that the interviews with students of special schools on the DVD were not viewed positively by students with lower support needs who usually attend special education units in mainstream schools. If we use this approach in the future, we would ensure that participants can identify themselves with the individuals used in the promotional materials.

We were attracted to school-based prevention research for adolescents as we could target a large proportion of the population
[32], but as others have reported, based on research with non-disabled adolescents, these studies are not without their problems
[29,30,32]. We believe some of the difficulties we experienced in gaining consent from parents and other carers may have been because research staff had no direct contact with families at this early stage of the trial. Fletcher and Hunter
[33] found that consent rates were low in classrooms that had teachers who were either invested minimally in the project or were new to schools. Many teachers, new to our schools at the beginning of the year, had been asked to teach the project at short notice and so may not have been as enthusiastic or prepared as their counterparts who had agreed to do so at the end of the previous year. In hindsight we would recruit in the first six months of the school year and introduce the *Ask Health Diary* and the CHAP in the second half of the year.

A further difficulty we experienced was the lack of control the researchers had over implementation. We provided the teacher with an *Ask Project Curriculum Strategy Booklet* which they used only as a guide, leading to substantial variation in the way the program was taught. This flexibility is appropriate in school settings because the teacher will need to adjust their approach based on their intimate understanding of the characteristic of their students.

We also found the diary was not always sent home at the appropriate time as 44% of the parents/carers of participants were not aware of the diary when contacted by research staff twelve months after it was scheduled to have been sent home from school. Anecdotal evidence suggests there was also less than optimal teacher-parent communication as to the purpose of the diary and the CHAP. Families often did not take the adolescent for the health review. The Carer exit survey may reveal other reasons for this, but if we were to repeat this study we would be in more constant contact with the teachers to ensure they complied with the protocol.

People with intellectual disability throughout the world are too often left behind in the progress that is made in improving the health of other citizens
[34]. Adolescents with intellectual disability face enormous difficulties in obtaining even the most basic health care. There are few avenues for them to become empowered and to improve and protect their own health. There are also too few GPs who have received adequate training in this area, and the health care system offers few incentives to ensure appropriate care for people with special needs
[18] Because of these factors, individuals with intellectual disability suffer health disparities, which must be addressed
[18,35-37]. This project seeks to achieve health gains with an intervention, which at its core empowers adolescents with intellectual disability (and their families) as they move towards the increased autonomy of adulthood. It is focused at a time when they are moving away from the relative protection of special education providers and targeted paediatric health services to limited and, possibly inadequately trained, generic health-care providers. This project seeks to demonstrate that the health of this population can be improved through: augmentation of communication and good advocacy; improved documentation of health problems; and improving access and quality of GP care. With an individualised health check and an individualised health advocacy diary for improving health care skills, the adolescent may gain a solid basis for, and an expectation of, good health care. These steps may not alleviate the all of problems but should pave the way to a noticeable improvement in both the processes and outcomes in health care.
